***Statistical analysis:***

Sample size: Based on previous studies in Ambanja (population of 28,468), Madagascar, we assume that the prevalence of CIN2+ lesions detected by D-VIA will be of 8% and of 4% by classical VIA interpretation. We have assumed 80% power at an alpha level of 0.05, using a 2-sided hypothesis. With this assumption, 1000 women will be needed.

Adequacy results: VIA and D-VIA results will be categorized as “satisfactory” (positive or negative) and “unsatisfactory”. Adequacy results (satisfactory or unsatisfactory) will be compared. Comparisons of percentages will be made between positive and negative VIA and positive and negative D-VIA. The McNemar’s test for comparisons and the Cohen’s kappa coefficient to measure reproducibility between VIA and D-VIA will be used.

Agreement results: Percentage of agreement will be calculated for each pair of on-site results and for distant D-VIA results by using McNemar’s test and adjust the p values with Bonferroni correction for multiple comparisons in order to overcorrect for Type I errors. Agreement of results will be also evaluated using Cohen’s kappa coefficient.

The following agreement results between assessors will be determined:

1) VIA results made by on-site health worker vs. distant expert D-VIA results

2) VIA results made by on-site expert vs. distant expert D-VIA results

3) VIA results made by on-site health worker vs. VIA results made by on-site expert

4) VIA results made by on-site health worker vs. on-site health worker’s D-VIA blinded results at 3 months

5) VIA results made by on-site expert vs. on-site expert D-VIA blinded results at 3 months

6) On-site health worker’s D-VIA blinded results at 3 months vs. on-site expert D-VIA blinded results at 3 months

7) On-site health worker’s D-VIA blinded results at 3 months vs. distant expert D-VIA results

8) On-site expert D-VIA blinded results at 3 months vs. distant expert D-VIA results

Accuracy: Sensitivities and specificities for the gold standard (cervical histology) will be obtained with the Smartphone diagnosis. Positive and negative predictive values will also be determined.

1. **Expected contribution**

Smartphone high-quality photographic technology has proven to be very useful in detecting pre- cancerous lesions on the cervix in a previous study that also took place in Madagascar.

Our expectation is that Teleconsultation and continuing education by mobile telemedicine will permit low-resource countries to introduce effectively and safely VIA as a triage test for those women for whom an HPV primary screening test is positive. An appropriate triage will reduce not only excessive referral rate but also an excessive delay giving the possibility of “screen (HPV), see (VIA/D-DIVA) and treat” program in a single or two visits.

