***Study design:***

This cohort study will be carried out in the Saint-Damien Health-Care Centre, in Ambanja, Madagascar. Women meeting the inclusion criteria will be invited to participate to the study after informed consent. Recruitment will be made during the month of July 2014.

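### The 1000 women stated for 80% power do not follow from 8% v 4% detection in the planned paired McNemar comparison, which needs 194 to 587 at alpha 0.05

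*Protocol*

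**What the plan says.** Under Statistical analysis, the protocol sets the effect: "we assume that the prevalence of CIN2+ lesions detected by D-VIA will be of 8% and of 4% by classical VIA interpretation". It then gives the error rates and the result: "We have assumed 80% power at an alpha level of 0.05, using a 2-sided hypothesis. With this assumption, 1000 women will be needed". No formula, discordant proportion, overlap between methods or allowance for loss is given.

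The same section names the test: "The McNemar’s test for comparisons and the Cohen’s kappa coefficient to measure reproducibility between VIA and D-VIA will be used". For agreement it lists eight pairs of assessments and applies a Bonferroni correction to the McNemar p values. It also plans sensitivity, specificity and predictive values against histology.

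The secondary outcome under Objective, and the Study procedure, make clear that both diagnoses are made on the same woman. The Inclusion Criteria require HPV-positive women aged 30-49 who attend one centre's screening programme. The flowchart (Annex 5.1) gives 30-69 years. Under Study design: "Recruitment will be made during the month of July 2014".

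**The concern.** In a paired comparison, two marginal rates do not fix the sample size. It also depends on how often the two methods disagree in the same woman, and the protocol does not say. That could be a mere omission, except that the margins themselves bound the disagreement tightly enough to test the stated number. The number fails that test.

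At stake is the protocol's only justification of its size. As written, the power figure belongs to no design that can be identified from the text. A reader cannot tell which comparison the 1000 women are meant to support, at which alpha, or what power the study has if fewer women have both readings.

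**Working it through.** **Inputs (Protocol, Statistical analysis).** D-VIA 8%, VIA 4%, so d = 0.04; two-sided alpha 0.05 (z = 1.96); power 80% (z = 0.8416); stated N = 1000.

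**1. Attempt to reproduce 1000 as two independent groups.**
n per group = [1.96·√(2·0.06·0.94) + 0.8416·√(0.08·0.92 + 0.04·0.96)]² / 0.04² = (0.6583 + 0.2817)² / 0.0016 = 552.2, so 553 per group.

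| Variant | Total N |
|---|---|
| Two-sided, pooled variance | 1,106 |
| Two-sided, continuity-corrected | 1,204 |
| Two-sided, unpooled | about 1,099 |
| Two-sided, arcsine | about 1,076 |
| One-sided (contradicts the text) | 870 |
| One-sided, continuity-corrected (contradicts the text) | 968 |
| One sample, 4% v 8% | 235 |

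With 500 per group the two-sided power is 76%. None of these gives 1000. A rounded two-group total is the nearest two-sided candidate, and it is the wrong design.

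**2. Bounds on discordance.** Let c be the proportion of women whose lesion is detected by both methods. Then D-VIA only = 0.08 − c, VIA only = 0.04 − c, and total discordance s = 0.12 − 2c. Because c lies between 0 and 0.04, s lies between 0.12 (no overlap) and 0.04 (every VIA detection is also a D-VIA detection).

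**3. Paired McNemar.** N = [1.96·√s + 0.8416·√(s − d²)]² / d².

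- s = 0.04: (0.3920 + 0.1649)² / 0.0016 = 193.8, so 194
- s = 0.12: (0.6790 + 0.2896)² / 0.0016 = 586.3, so 587

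Power at 1000 = Φ{[d√1000 − z·√s] / √(s − d²)}. For s = 0.12 at 0.05 this is Φ{(1.2649 − 0.6790) / 0.3441} = Φ(1.70) = 0.956.

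| Overlap | s | N at 0.05 | Power at 1000 | N at 0.05/8 | Power at 1000 |
|---|---|---|---|---|---|
| Nested | 0.04 | 194 | >99.9% | 317 | >99.9% |
| Half of VIA detections shared | 0.08 | 391 | 99.4% | 637 | 96.0% |
| Independent readings | 0.1136 | 555 | 96.5% | 905 | 84.8% |
| None | 0.12 | 587 | 95.6% | 957 | 82.2% |

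With continuity correction the range is 242 to 636 at 0.05 and 365 to 1,006 at 0.05/8. The exact conditional test at s = 0.12 gives 95.1% and 80.9% power at 1000.

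**4. What would make 1000 right at 0.05?** Solving the formula for N = 1000 gives s = 0.204. The margins cap s at 0.12, so this cannot occur.

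**5. Recruitment (range under assumptions only).** 1000 / 31 days is about 32 women a day. Assume half of the town's 28,468 people are female and 15% to 30% of those are aged 30-49: that is 2,135 to 4,270 women. Reaching 1000 would then need HPV positivity of 47% (1000/2,135) down to 23% (1000/4,270), with everyone screened and consenting.

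**The case against.** The strongest reply is that the error is on the safe side and that 1000 may suit the plan anyway. At 0.05, 1000 pairs give about 96% power or more. At the Bonferroni level of 0.00625, 1000 lies just above the no-overlap requirement of 957 and leaves a little room for unsatisfactory readings. Precision also argues for a larger number. Assuming 10% CIN2+ and 80% sensitivity, the 95% confidence interval for sensitivity has a half-width of 1.96·√(0.8·0.2/100), about 8 points, at 1000 women, against about 10 at 587 and 18 at 194. No planned analysis becomes invalid.

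Most of this stands as a reason to keep the size. It does not rescue the calculation: the sentence states 0.05 and mentions neither Bonferroni nor precision. Even at 0.00625, 1000 is reached only with continuity correction and with D-VIA finding none of the lesions that VIA finds.

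Three stronger readings are tempting, and the documents do not support them.

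- **Enrolment must be cut because women are biopsied needlessly.** This treats 587 as conservative. It is so only at 0.05, and accuracy against histology is also an aim.
- **The study is underpowered because 1000 means women screened.** At an assumed 20% to 40% HPV positivity, the resulting 200 to 400 pairs would have 37% to 81% and 64% to 98% power respectively at 0.05. But the entry criterion is HPV positivity, the text nowhere says that 1000 counts women screened, and no positivity rate is given.
- **1000 women cannot be recruited in July 2014.** HPV positivity, age structure, catchment and the size of the prescreened pool are not given. Eligibility depends on attending the programme, not on living in the town, and the abstract describes the women as already prescreened, so positives may have accumulated before July.

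**Conclusion.** The point holds for the sample-size statement. On the protocol's own inputs, the planned paired test needs 194 to 587 women at 0.05, not 1000, and 1000 pairs would have about 96% to over 99.9% power, not 80%. This needs no outside figure, because the whole admissible range of discordance was covered. It rests on the usual normal approximation for McNemar's test; continuity correction or the exact test shifts the figures slightly and changes nothing.

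The Bonferroni figures (317 to 957 women; 82% to over 99% power at 1000) additionally assume that the 8% and 4% margins apply to the agreement pair in question.

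On recruitment, the conclusion is limited: the documents do not show that 1000 HPV-positive women are attainable at one centre in one month. That is a gap in the justification, not a demonstrated shortfall. The two age ranges (30-49 and 30-69) leave the eligible pool unsettled.

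**What to change.** Replace the sample-size paragraph with a McNemar calculation that states:

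- the 8% and 4% detection rates and the assumed discordant proportion, with a reason for it;
- the comparison supported and its alpha (0.05, or 0.05/8 if it is one of the Bonferroni-adjusted pairs);
- the unit: HPV-positive women with both readings;
- either the required number (194 to 587 at 0.05; 317 to 957 at 0.05/8) or the power that 1000 women deliver (at least about 96% at 0.05; at least about 82% at 0.05/8).

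If 1000 is kept, say why, for example the adjusted tests or the precision of sensitivity. Also state the HPV positivity, catchment and prescreened pool behind the recruitment target, and give the power at the number expected by the end of July 2014. Reconcile the age range in the Inclusion Criteria with the one in the flowchart.

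The cost is one rewritten paragraph and one corrected age range. No change to enrolment is required by this point alone.

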Primary outcomes:

1) To evaluate if a Smartphone may assist health-care worker (in-site) for cervical cancer screening;

2) To evaluate how the expert at a distant location (off-site) may improve VIA results.

Secondary outcomes:

1) To assess the agreement between diagnoses based on the visualization of the cervix with the unaided eye, after the application of 5% acetic acid (control) during a patient clinical consultation and diagnoses for the same patient based on evaluation of Smartphone photos.

1. **Material and method**

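### The protocol ties percentage of agreement to Bonferroni-adjusted McNemar tests, which test equal positivity rather than agreement, and sets no rule for a conflict with the planned kappa

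*Protocol*

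**What the plan says.** Agreement between naked-eye and smartphone-photo diagnoses is the secondary outcome (Protocol, Objective): "To assess the agreement between diagnoses based on the visualization of the cervix with the unaided eye", set against diagnoses for the same patient from the photographs.

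The analysis is in Protocol, Statistical analysis, under Agreement results:
- The method: "Percentage of agreement will be calculated for each pair of on-site results and for distant D-VIA results by using McNemar’s test".
- The p values: the plan will "adjust the p values with Bonferroni correction for multiple comparisons in order to overcorrect for Type I errors".
- A second measure: "Agreement of results will be also evaluated using Cohen’s kappa coefficient".
- The scope: "The following agreement results between assessors will be determined", followed by a list of eight pairs of readings.

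The section gives no kappa target, no rule for reading a non-significant McNemar result, and no divisor for the Bonferroni correction. The preceding paragraph, Adequacy results, assigns McNemar's test to comparisons and kappa to reproducibility. The Abstract names kappa, McNemar's test and Bonferroni's adjustment together as the means of assessing D-VIA.

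**The concern.** Percentage of agreement is the share of women on whom two readings coincide. McNemar's test ignores those women. It looks only at the two kinds of disagreement and asks whether they are equally frequent. Readers who disagree often, but evenly in both directions, give a large p value. Readers who almost always agree, but whose few disagreements lean one way, give a small one. A test with these properties cannot stand as the method for percentage of agreement.

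The direction of the correction adds to the difficulty. Bonferroni guards against falsely declaring a difference. It gives no protection against falsely declaring agreement. Anyone who took non-significance as agreement would find that conclusion easier to reach after the correction. At stake is what can be concluded on the secondary outcome across the eight listed pairs.

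**Working it through.** **Inputs.** From the Protocol, Statistical analysis: two-sided alpha 0.05, 1000 women and eight listed pairs. The divisor of eight is an assumption taken from that list; it gives a per-test level of 0.05/8 = 0.00625. The protocol gives no agreement figure to reproduce. The 1000 serves only as the table total, and nothing below depends on how it was derived. All tables are assumed.

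**Formulas.** Cells: a both positive, b first reader only, c second reader only, d both negative; N = a + b + c + d.
- Percent agreement: po = (a + d)/N.
- Chance agreement: pe = p1·p2 + (1 − p1)(1 − p2), with p1 = (a + b)/N and p2 = (a + c)/N.
- Kappa = (po − pe)/(1 − pe).
- Exact McNemar: p = 2·P(X ≤ min(b, c)), X ~ Binomial(b + c, 0.5), capped at 1. Cells a and d do not enter.
- Positive specific agreement: 2a/(2a + b + c). Negative: 2d/(2d + b + c).

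**Table 1: independent readers, each 20% positive (40/160/160/640).**
- po = 680/1000 = 68%.
- pe = 0.2 × 0.2 + 0.8 × 0.8 = 0.68, so kappa = 0.
- Positive specific agreement = 80/400 = 20%; negative = 1280/1600 = 80%.
- Discordant cells 160 v 160: McNemar p = 1.

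**Table 2: near-perfect readers (75/15/1/909).**
- po = 984/1000 = 98.4%.
- pe = 0.090 × 0.076 + 0.910 × 0.924 = 0.84768; kappa = (0.984 − 0.84768)/0.15232 = 0.89.
- Positive specific agreement = 150/166 = 90%; negative = 1818/1834 = 99%.
- Discordant cells 15 v 1: p = 2 × (1 + 16)/2^16 = 0.0005; times eight = 0.004.

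The test is significant for the pair that agrees well and gives p = 1 for the pair that agrees only by chance. In each table it answers its own question correctly: positivity is equal in Table 1 and differs (9.0% v 7.6%) in Table 2.

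**Effect of the correction.** With 100 discordant pairs, the exact two-sided p values are:

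| Split | p | Below 0.05 | Below 0.00625 |
|---|---|---|---|
| 60/40 | 0.057 | no | no |
| 61/39 | 0.035 | yes | no |
| 64/36 | 0.0066 | yes | no |
| 65/35 | 0.0035 | yes | yes |

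The split needed for significance moves from 61/39 to 65/35. As a single-table example, 30/50/30/890 has 92% agreement and kappa (0.92 − 0.8696)/0.1304 = 0.39. Its raw p is 0.033, and 0.26 after multiplication by eight.

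**Missed differences.** Approximate power = Φ[(δ√N − z√π)/√(π − δ²)], where δ is the true difference in positivity, π the proportion discordant, and z = 1.960 at 0.05 or 2.734 at 0.00625. With N = 1000, δ = 0.02 and π = 0.08, the chance of a non-significant result rises from 39% to 69%.

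**The case against.** The strongest reply is that this is loose drafting. Kappa is planned in the very next sentence, and the Abstract lists it first. The Adequacy paragraph already separates the two tools correctly. Read with it, the disputed sentence may only mean that percentages will be reported and the pairs also compared by McNemar's test. In Table 1 the plan's own outputs, 68% and kappa 0, would stand beside p = 1 and expose the problem. Confidence intervals and similar reporting detail may be in a SAP that is not shown. Bonferroni is a valid if conservative correction for difference tests. At N = 1000 and a level of 0.00625, power for a 4-point difference in positivity is still 82% at the largest discordance compatible with rates of 8% and 4% (π = 0.12).

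Much of this stands, and it rules out three stronger readings that a reader might infer.
- That agreement will be judged by McNemar's test alone. It will not; kappa is planned.
- That the protocol will declare agreement from non-significance. No sentence says so. The wording on Type I errors fits ordinary difference testing at least as well.
- That the sample-size rates supply the protocol's own case of good agreement wrongly rejected. Those rates are described as "the prevalence of CIN2+ lesions detected by D-VIA will be of 8% and of 4% by classical VIA interpretation", so they are lesion detection rates, not reader positivity. A table with one set of positives nested in the other (40/40/0/920) would need a further assumption. There the test would also be right to reject, since one reading calls twice as many women positive and positive specific agreement is 80/120 = 67%.

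What the reply does not remove is the sentence itself. It names a test as the method for a quantity which that test does not produce, and it leaves open which result governs when p value and kappa point in opposite directions.

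**Conclusion.** The statement is wrong under any reading: percentage of agreement cannot be calculated by McNemar's test, and the test's p value is not evidence on agreement. Tables 1 and 2 show that p value and kappa can point in opposite directions (kappa 0 with p = 1; kappa 0.89 with an adjusted p of 0.004). The planned kappa limits the harm, and the affected outcome is the secondary one; sensitivity, specificity and predictive values against histology do not depend on this sentence.

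The claim that the correction favours a finding of agreement is conditional. It holds only if non-significance is read as agreement, which the protocol neither states nor excludes. Its size (65/35 instead of 61/39) also assumes eight as the divisor and 100 discordant pairs. For tests of difference, the correction errs in the usual conservative direction. The point is worth correcting, but it does not undermine the design.

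**What to change.** Rewrite the Agreement results paragraph:
- For each of the eight pairs, assess agreement by overall percent agreement, positive and negative specific agreement, and the already planned kappa, each with a 95% CI and without multiplicity-adjusted p values.
- Restrict McNemar's test to the difference in positivity between two readings, reported with the paired difference and its 95% CI.
- State that a non-significant McNemar result is not evidence of agreement.
- If the McNemar tests are adjusted, name the number of tests and use Holm, which controls the same familywise error and is never less powerful than Bonferroni. This last change is a refinement; Bonferroni is not an error.

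The cost is the wording of one paragraph. The data collected and the sample size stay as they are.

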**Abstract**

**Background:** Cervical cancer is the leading cause of cancer death in females in Madagascar. In this country, a large-scale screening of precancerous lesions with cytology is hardly possible, because of the lack of specialists and infrastructures. Visual inspection of the cervix with application of 5% acetic acid (VIA) is an inexpensive alternative but very subjective since it depends on the examiner’s experience. Mobile telemedicine is a very promising tool in order to assist non-expert health-care workers in rural area for cervical cancer screening.

**Objective:** To assess if Smartphone may assist health-care worker (on-site) and to evaluate the diagnostic reliability and accuracy of cervical examination with smartphone photos of VIA (D-VIA) compared with conventional VIA, for women testing positive for human papillomavirus (HPV).

**Material and method:** On-site health care workers will be trained in VIA. Prescreened HPV-positive women will be referred to VIA evaluation, during which digital images with a smartphone (D-VIA) will be taken for later evaluation by a VIA specialist in Geneva linked by telemedicine. Women with positive VIA results will be treated with cold coagulation if eligible. Histological results will be considered as gold standard. The results will be analyzed with Cohen’s kappa coefficient, Mcnemar’s test and Bonferroni’s adjustment for multiple comparisons to assess the performance of D-VIA.

**Expected results:** Based on the results of this project, we will develop an educational training and quality assurance program for health providers for VIA and so contribute to a scaling-up of cervical cancer control. An appropriate triage by VIA will reduce not only an excessive referral rate but also an excessive treatment delay, giving the possibility of a “screen (HPV), see (VIA/D-VIA), and treat” program in a single or two visits.

**Key words:** Cervical cancer; HPV; VIA; screening; smartphone; telemedicine

1. **Introduction**

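### Bonferroni is applied to the eight McNemar comparisons with over-correction as the stated aim; Holm's step-down procedure gives the same family-wise control and a small gain in power at no cost

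*Protocol*

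**What the plan says.** Under Agreement results in the Statistical analysis section, the protocol states "Percentage of agreement will be calculated for each pair of on-site results and for distant D-VIA results by using" McNemar's test, and adds that it will "adjust the p values with Bonferroni correction for multiple comparisons in order to overcorrect for Type I errors". Eight numbered assessor pairs follow, ending with "8) On-site expert D-VIA blinded results at 3 months vs. distant expert D-VIA results". The Abstract repeats the method as "Bonferroni’s adjustment for multiple comparisons to assess the performance of D-VIA", without a word about over-correction.

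Neither place gives the divisor or a family-wise error level. The only alpha is in the sample-size paragraph: "We have assumed 80% power at an alpha level of 0.05, using a 2-sided hypothesis". That paragraph assumes that "the prevalence of CIN2+ lesions detected by D-VIA will be of 8% and of 4% by classical VIA interpretation" and concludes "With this assumption, 1000 women will be needed". The threshold of 0.05/8 and the 5% family-wise level used below are therefore inferred from the list and from the sample-size alpha.

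**The concern.** A multiplicity adjustment should hold the family-wise error at a stated level. Going beyond that level protects no one and costs power, yet here the excess is given as the purpose.

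Bonferroni tests all eight pairs at the strictest threshold, whatever the other tests show. If some pairs truly differ, and the sample-size paragraph expects VIA and D-VIA to differ, fewer than eight true null hypotheses remain and part of the permitted error goes unused. Holm's procedure recovers some of it without any new assumption. At stake is the chance of missing real differences between readers or between direct inspection and photographs.

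**Working it through.** **Inputs from the protocol.** Eight listed comparisons; 4% for VIA and 8% for D-VIA; 1000 women; two-sided alpha 0.05; 80% power.

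**Assumed.** The 4% and 8% are used as the rates of positive readings. The correlation between readings is not given, so a one-factor latent normal model is run with correlation 0 to 0.8.

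**1. The protocol's own figure.** For two independent proportions, n per group = (1.96·√(2·0.06·0.94) + 0.842·√(0.08·0.92 + 0.04·0.96))² / 0.04² ≈ 553, or 1106 in total. For paired readings, n = (1.96·√s + 0.842·√(s − d²))² / d², with d = 0.04 and s the discordant share. Rates of 8% and 4% allow s from 0.04 to 0.12, which gives n from 194 to 587. The stated 1000 is not reproduced, but it exceeds what the paired test needs. That is a separate matter; the 1000 is taken as given below.

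**2. One test under Bonferroni.** The threshold is 0.05/8 = 0.00625 (z = 2.734). Power = Φ[(d·√1000 − z·√s)/√(s − d²)]. In the least favourable case, s = 0.12:
- at 0.05: (1.265 − 0.679)/0.344 = 1.70, power 95.6%;
- at 0.00625: (1.265 − 0.947)/0.344 = 0.92, power 82.2%.

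So a full 4-point difference keeps more than the planned 80% even under Bonferroni.

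**3. Thresholds.** Holm orders the eight p values and compares the i-th smallest with 0.05/(9 − i), stopping at the first failure: 0.00625, 0.00714, 0.00833, 0.0100, 0.0125, 0.0167, 0.025, 0.05. The first step equals Bonferroni's threshold and every later step is looser. Holm therefore rejects all that Bonferroni rejects and sometimes more.

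**4. Structure.** The eight pairs come from five readings per woman: VIA by the health worker, VIA by the on-site expert, D-VIA by the distant expert, and two D-VIA readings at three months. With 4% for both VIA readings and 8% for all three D-VIA readings, comparisons 1, 2, 4 and 5 are true differences, and 3, 6, 7 and 8 are true nulls.

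**5. Simulation at the protocol's rates** (1000 women, asymptotic McNemar, 20,000 runs per setting; Bonferroni → Holm):

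| Correlation | Average power, four true differences | Power to reject all four |
|---|---|---|
| 0 | 85.1% → 87.9% | 59.4% → 67.3% |
| 0.3 | 89.6% → 91.7% | 70.0% → 76.3% |
| 0.6 | 95.8% → 97.0% | 86.2% → 90.2% |
| 0.8 | 99.3% → 99.6% | 97.4% → 98.5% |

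The average gain is 0.3 to 2.8 points; the gain for all four is 1.1 to 7.9 points. Power to reject at least one is identical. A separate run gave average power of 93.2% → 94.7% at correlation 0.5 and 98.9% → 99.3% at 0.8.

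**6. Family-wise error.** With the four true nulls above, it is 2.2 to 2.4% for Bonferroni and 3.6 to 4.4% for Holm. With all five rates equal, it is 3.8 to 4.3% for both methods (about 3% with exact McNemar). All are below 5%.

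**7. If smaller differences exist.** Rates of 4% and 6% for the two VIA readings, 8% for the distant D-VIA, and 6% and 8% for the three-month D-VIA readings are an assumption, not the protocol's. With exact McNemar, average power over the true differences is 32.0% → 35.7% at correlation 0.5 and 46.4% → 53.0% at 0.8, gains of 3.7 and 6.6 points. The asymptotic test gives 36.1% → 39.8% and 50.2% → 58.1%, gains of 3.7 and 7.9 points.

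**The case against.** The strongest reply is that Bonferroni is a valid and common choice, that a step-down refinement could be left to a statistical analysis plan, and that the over-correction wording may be a slip, since the Abstract does not carry it. Agreement between direct inspection and photographs is a secondary outcome, and percentage agreement and kappa do not depend on the adjusted threshold. All of this stands, and it keeps the point minor. It does not remove it: the protocol itself fixes the method and gives a reason for it that no error-control goal supports.

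A reader might infer three stronger things that the protocol does not support.

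- *That the comparisons are badly underpowered, at 32 to 53%.* Those figures need the assumed 6% rates. At the protocol's 4% and 8%, average power under Bonferroni is already 85% or more.
- *That Holm cures the gap between the 0.05 used for sample size and the 0.00625 used for testing.* Holm's first threshold is also 0.00625.
- *That the loss comes from dependence among tests sharing readings, and that Holm recovers it.* Holm stays valid under dependence but does not exploit it. When no pair differs, both methods have the same family-wise error, about 3 to 4%.

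**Conclusion.** The point holds as a minor efficiency and wording matter. Bonferroni is valid here but needlessly conservative once any comparison has been rejected. Holm gives the same 5% family-wise control under any dependence and never rejects fewer hypotheses.

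At the protocol's rates and 1000 women, Holm adds about 0.3 to 3 points of average power, and about 1 to 8 points for rejecting all four VIA versus D-VIA pairs. If 2-point differences between readers exist, the average gain is about 3.5 to 6.5 points with the exact test, and close to 8 in the most favourable asymptotic setting. The chance of finding at least one difference is unchanged.

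These sizes rest on three assumptions: the correlation between readings, the use of 4% and 8% as rates of positive readings, and a family of eight at two-sided 0.05. The ranking of the two methods does not depend on them. Nothing here invalidates the planned analysis.

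**What to change.** In the Abstract and under Agreement results in the Statistical analysis section, replace Bonferroni with: *Holm step-down adjustment over the eight listed comparisons, family-wise two-sided 0.05*. Delete the clause that gives over-correction as the aim. The sponsor should first confirm the family of eight and the 5% level, because the protocol states neither for these tests.

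The cost is one sentence in each of two places, with no extra data and no loss of error control. If the sponsor prefers to keep Bonferroni, the clause should still go, and the family and level should still be stated. The relation between the sample-size alpha and the testing threshold needs its own sentence either way.
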